### Interim analyses {21b}

An interim analysis will be fulfilled when half of the patients (829) have been included to possibly prematurely stop the trial, based on the primary outcome, according to O’Brien Fleming Alpha Spending function method. The research will be stopped if the interim analysis demonstrates the efficacy of one of the arms being treated or due to futility. This analysis will be performed to ensure that there is no major imbalance of efficacy or tolerance (mortality and serious adverse effects surgical postoperative complications) between the two groups. The steering committee will discuss the discontinuation of the study in case of imbalance between postoperative gastric leak rate in each arm (if postoperative gastric leak rate is 5% higher in the experimental group compared to the control group).

### Methods for additional analyses (e.g. subgroup analyses) {20b}

Not applicable.

### Methods in analysis to handle protocol non-adherence and any statistical methods to handle missing data {20c}

Analysis will be performed on the intention-to-treat population. Methods used to handle missing data will be described fully in the study report.

### Plans to give access to the full protocol, participant-level data and statistical code {31c}

N/A

## Oversight and monitoring

### Composition of the coordinating centre and trial steering committee {5d}

The trial steering committee is chaired by the lead principal investigator for the study and includes the scientific director, the executive manager of the clinical research unit, a surgeon, an anaesthesiologist, a statistician and project management staff. The committee is responsible for drafting and amending the protocol and other key trial documents; monitoring recruitment, data entry completion and quality; and drafting and approving the statistical analysis plan and other trial publications. The steering committee will meet every 6 months during the recruitment period and at least once a year during the follow-up period. The committee will be consulted by the sponsor when the results of the intermediate analysis will be available. Actions will be proposed if necessary and the sponsor will communicate its final decision.

### Composition of the data monitoring committee, its role and reporting structure {21a}

This trial compares standard care *versus* experimental bougie during LSG. The bougie diametre does not change intraoperative or postoperative management nor the method for diagnosis of gastric leak. Besides, the experimental device is classified IIa, CE-marked, and has already been used for sleeve gastrectomy in previous essays. In view of the minimal risks arising from this research, it was not considered necessary to establish an independent data monitoring oversight committee. Nonetheless, the investigator will notify the sponsor without delay in case of serious adverse events. The sponsor will report to the French national safety agency without delay any serious adverse event possibly related to the usage of the experimental bougie.

### Adverse event reporting and harms {22}

Serious adverse events (SAEs) that are considered related to the study are monitored and reported without delay. SAEs related to the implementation action of the experimental medical device include perforation of the oesophagus or the stomach during bougie introduction, stapling and/or section of the bougie with the stapling device, impossibility to remove the bougie and staple-line opening during bougie removal. Study-specific reportable adverse events, including death, or resulting in a life-threatening situation or significant disability, or requiring inpatient hospitalization or prolongation of existing hospitalization are also being monitored during the trial.

All SAEs and reportable adverse events must be recorded in the CRF. The severity of adverse events is assessed according to the Dindo-Clavien classification of surgical complications [13].

### Frequency and plans for auditing trial conduct {23}

GCP compliance monitoring is being conducted by the sponsor. Risk-based monitoring is in place for the study. All data, documents and reports may be subject to regulatory audits and inspections.

### Plans for communicating important protocol amendments to relevant parties (e.g. trial participants, ethical committees) {25}

All protocol amendments will be approved by responsible independent ethics committees and local sites prior to implementation. Protocol amendment of August 5, 2020, has required re-consent from 1 participant of the study.

### Dissemination plans {31a}

Trial findings will be disseminated at national and international scientific meetings, by publication in a scientific journal. Authorship for all trial publications will be based on criteria formulated by the International Committee of Medical Journal Editors, available at www.icmje.org.

## Discussion

Surgical strategies that reduce the risk of gastric leak after LSG have the potential to improve postoperative outcomes and reduce costs. This multicentre, prospective, randomized, single-blind, pragmatic trial has been designed to determine whether the diametre of the bougie used to calibrate the remnant stomach during LSG is important, specifically whether the use of a 48-Fr bougie decreases the rate of postoperative gastric leak. Given that the use of a calibration bougie is an international standard, evidence for the superiority of a 48-Fr bougie over a smaller diametre standard care bougie from this trial would provide strong justification for a change in surgical practices. Considering the large sample size and the scarcely restrictive eligibility criteria, a generalizability of results is expected to other populations undergoing LSG. A finding of no significant difference between the groups for the primary and key secondary outcomes would imply that any benefit with the use of a 48-Fr bougie does not exist, or is not clinically important for the majority of patients undergoing LSG. Regardless, BOUST will provide data on the safety of larger diametre calibration bougie, particularly in relation to intraoperative complications.

In line with the pragmatic study design, and to promote the recruitment of a large number of participants and the generalizability of the trial results, eligibility criteria were designed to enrol a large range of patients. It is estimated that more than 90% of patient candidates for LSG are eligible for this study. Trial processes have been designed to be in line with routine clinical care at participating centres, enabling surgeons to easily enrol and monitor their patients without the presence of research staff. All data collected, apart from the quality of life questionnaires, are already routinely collected. No additional laboratory tests or procedures are required for the trial.

In the protocol for BOUST originally approved by ethics committee, before the enrolment started (protocol version 1.0, 10 June 2016), the operating surgeon was kept blinded of the diametre of the calibration bougie inserted by the anaesthesiologist. Considering that the surgeon would become aware of which bougie is used, either by direct visualization of the bougie in the operating room or its shape in the empty stomach, the study protocol was amended in 2019 (protocol version 2.0, 5 August 2019) to change the double-blind design to a patient-blind design. This change aligns with standard practice, since the bougie diametre is routinely determined by the surgical team and the patient is generally unaware of the diametre of the bougie used.

There are some limitations that need to be considered. By opting for a pragmatic design, BOUST does not mandate any specific methods to use during the perioperative period or during surgery that could impact the risk of postoperative gastric leak, including the diametre of the standard care bougie. Several other surgical methods have been advocated (distance between the staple-line and the pylorus, buttressing material or suture of the staple-line, staple heights) but none has demonstrated a decrease of gastric leak rate [3]. However, these technical modalities of LSG are standardized in each study site and stratified randomization by centre will be carried out. Mid-term weight loss evolution is a key secondary outcome of the study. A concern of bariatric surgeons and patients is that the use of a larger bougie could lead to long-term (> 5 or 10 years after LSG) weight regain. Although BOUST was designed to analyse the effect of the bougie diametre on the primary outcome, this trial will be, to our knowledge, the largest randomized study to report the outcomes of the calibration bougie diameter on mid-term weight loss. Longer-term follow-up studies may help determine if a larger calibrated sleeve is associated with weight regain.

In conclusion, BOUST is an ongoing, randomized, controlled, pragmatic trial that will provide the most definitive comparative data to date on the risk of gastric leak after LSG using 48-Fr vs. 34–38-Fr calibration bougie. If the hypothesis that 48-Fr bougie is superior to 34–38-Fr bougie is proven, this will provide an important strategy to improve LSG outcomes, which can be rapidly implemented into clinical practice.

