## Introduction

### Background and rationale {6a}

Laparoscopic sleeve gastrectomy (LSG) has become an increasing bariatric procedure, mostly because of its relative simplicity and efficacy. Approximately 27,500 LSGs were performed in France in 2014 [1] and 125,000 in the USA in 2016 [2]. The basic principle is to create a narrow stomach along the lesser curvature, using a calibration bougie as a template to perform a vertical partial gastrectomy, resecting the greater curvature and fundus of the stomach. The most common complication is gastric leak resulting from staple-line leakage, observed in approximately 3% of cases [3]. Gastric leak is most often diagnosed within 5 days after surgery, but late presentations are described. Treatment of this complication is usually long and incapacitating, requiring surgical, radiological or endoscopic drainage and parenteral or enteral nutritional support. Controversy is ongoing about potential options that might reduce the risk of gastric leak, and among them the diametre of the bougie used to calibrate the remnant stomach’s volume. The issue is whether a sleeve gastrectomy with a smaller diametre is associated with greater weight loss at the expense of a higher rate of postoperative leak.

In a meta-analysis published in 2013 [3], the use of a bougie diametre larger than or equal to 40-French (Fr) and under 50-Fr was correlated with a decrease in the rate of leak, without lowering weight loss at 3 years. Most teams use a bougie diametre of less than 40-Fr [3], mainly 36-Fr [4], in order to reduce the risk of long-term weight regain. However, concerns of bariatric surgeons whether the use of a larger bougie could lead to weight regain [5] appear to be unfounded in the literature [3, 6]. Conversely, the use of a bougie larger than 45-Fr allows reduction of gastric leak rate to 0.92–1.7% [3, 6]. Indeed, no prospective randomized study was ever conducted to investigate the impact of the diametre of the calibration bougie on the rate of postoperative gastric leak. The main aim of this study is to show a reduction of postoperative gastric leak rate with the use of a 48-Fr diametre calibration bougie during LSG in comparison with the use of a smaller standard care bougie.

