### Sample size {14}

The sample size for the trial (1658 participants) is based on a comparison between two independent groups of the proportions of participants experiencing the primary outcome measure of postoperative gastric leak. We made the hypothesis of a difference of postoperative fistula rates of 3% with a standard care calibration bougie and 1% with a 48-Fr calibration bougie. Considering a bilateral alpha risk of 5% and a power of 80%, we would need to include 1576 patients (788 in each group). A 5% rate of participants lost to follow-up is estimated; therefore, 1658 patients will be included (829 in each group).

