## Statistical methods

### Statistical methods for primary and secondary outcomes {20a}

Analyses will be by intention to treat. The impact of the bougie calibration diametre, 48-Fr versus 34- to 38-Fr, on the primary outcome of postoperative gastric leak rate during the first postoperative month will be analysed using a logistic regression model, with group, and stratification factors (centre, gender, super-obesity). The primary comparison will be a two-sided test at the 5% significance level. The impact of the bougie calibration diametre on secondary outcomes will be analysed using statistical methods appropriate for the type of outcome. Logistic regression will be used in a multivariate model to identify factors independently associated with morbidity. The normal distribution will be tested using the Shapiro-Wilk test. Should this be significant at the 5% level, a non-parametric approach (Mann-Whitney test) or variable transformation will be used.

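### The Discussion reads a non-significant result as absence of a clinically important benefit, which a superiority test sized for 3% vs 1% cannot support

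*Protocol article*

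**What the plan says.** The Discussion states in advance how a null result is to be read. If the groups do not differ significantly on the primary and key secondary outcomes, this "would imply that any benefit with the use of a 48-Fr bougie does not exist, or is not clinically important". The sentence limits itself to the majority of LSG patients.

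Three other places bear on it:

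- **Sample size {14}** assumes leak rates of "3% with a standard care calibration bougie and 1% with a 48-Fr calibration bougie". For a two-sided 5% test with 80% power it asks for 1576 patients, 788 per arm, raised to 1658 for 5% loss to follow-up.
- **Background and rationale {6a}** puts the general leak rate after LSG at about 3% and says that "the use of a bougie larger than 45-Fr allows reduction of gastric leak rate to 0.92–1.7" per cent.
- **Statistical methods {20a}** says: "The primary comparison will be a two-sided test at the 5% significance level". Trial design {8} calls the trial a superiority trial.

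The article ties the null conclusion to significance alone, not to a confidence interval or a smallest important reduction.

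**The concern.** Failing to reject equality is not evidence that the rates are equal, or that their difference is too small to matter. The Discussion treats it as such. Whether that does harm depends on how often a reduction worth having would come out non-significant, and on whether the interval around such a result would still contain it. The article supplies the figures for both checks: a design effect of 2 points and a range of leak rates for large bougies that reaches well above the 1% used for sizing.

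The stake is the trial's message. The article describes leak treatment as long and incapacitating, and expects the trial to give the most definitive comparison so far. If the sentence is followed, an inconclusive trial could be reported as showing that the larger bougie brings no worthwhile protection.

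**Working it through.** **Inputs.** Control rate p1 = 3% and planned 48-Fr rate 1% (Sample size {14}); n = 788 per arm, two-sided α = 5% (same section); leak rates of 0.92% to 1.7% for bougies above 45-Fr (Background {6a}). Pairing 1.7% with a 3% control rate is an assumption: 3% is the article's planning value for control, but 3% vs 1.7% is not reported there as a single comparison.

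**1. The plan's own figure.** The pooled-variance formula for two proportions gives 769 per arm for 3% vs 1% at 80% power (866 with continuity correction), against the stated 788, a difference of about 2.4%. For loss to follow-up, 1576 / 0.95 = 1658.9, against the stated 1658. The sample size is sound for its own inputs.

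**2. Power at other true rates.** With d = p1 − p2 and p̄ = (p1 + p2)/2,

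se0 = √[2p̄(1 − p̄)/n], se1 = √[p1(1 − p1)/n + p2(1 − p2)/n], power = Φ[(d − 1.96·se0)/se1].

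- At p2 = 1.0%: d = 0.020, se0 = 0.00705, se1 = 0.00704; power = Φ(0.878) = 81%.
- At p2 = 1.7%: d = 0.013, se0 = 0.00763, se1 = 0.00762; power = Φ(−0.257) = 40%.

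| True 48-Fr rate (control 3%) | Power, 788 per arm | Non-significant |
|---|---|---|
| 0.92% (lower end cited) | 85% | 15% |
| 1.0% (planned) | 81% | 19% |
| 1.31% (midpoint of range) | 64% | 36% |
| 1.5% | 52% | 48% |
| 1.7% (upper end cited) | 40% | 60% |

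Power falls below 50% above about 1.53%. With all 829 per arm analysed, power at 1.7% is 42%. Exact enumeration with 788 per arm gives 83% at 1.0% and 40% at 1.7% for the chi-square test, and 78% and 34% for Fisher's test. These figures ignore the adjustment for stratification factors and the O'Brien-Fleming interim look, which would lower final power slightly.

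**3. What a non-significant result can look like.** Take 24 leaks in 788 (3.05%) vs 13 in 788 (1.65%).

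- Difference = 1.40 points; p̄ = 2.35%; se0 = 0.00763; z = 0.01396 / 0.00763 = 1.83; p = 0.067.
- Unpooled se = 0.00762; 95% CI = 1.40 ± 1.96 × 0.762 = −0.1 to +2.9 points.

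The interval contains the planned 2-point reduction, yet the Discussion would allow this result to be read as no benefit, or none of importance. With one leak fewer in the 48-Fr arm (24 vs 12), p = 0.043 and the result is significant.

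**4. A null result that is informative.** If both arms show 2%, the half-width is 1.96 × √(2 × 0.02 × 0.98 / 788) = 1.4 points. That interval excludes a 2-point reduction but not one of 1.3 points (3% to 1.7%). The interval separates this case from the one in step 3. The significance test does not.

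**The case against.** The case on the other side has several parts.

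*The sentence is qualified.* It requires null findings on key secondary outcomes as well, and speaks only of the majority of patients. This is true, and any account of the sentence should say so. It does not repair the inference. Non-significance on weight loss or quality of life says nothing about leak, and a complication expected in about 3% cannot concern a majority whatever the bougie does.

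*Reductions below 2 points may not matter.* The article does not say this. It presents 3% vs 1% as a hypothesis, not as a smallest important difference. Even with 2 points as the threshold, the 24 vs 13 result does not exclude it.

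*The 40% is the least favourable endpoint and depends on the control rate.* This stands. At a true 48-Fr rate of 1.7%, illustrative control rates of 3.5% and 4.0% would give power of 61% and 78%; a rate of 2.5% would give 20%. A reader might infer that true effects within the cited range would usually be missed. The documents do not support that: power exceeds 50% over roughly the lower four-fifths of the range and is 64% at its midpoint.

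*Some null results would be conclusive.* This also stands. A reader might infer that no null result from this trial could be informative, but 2% vs 2% would rule out the planned effect.

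*It is Discussion text, and interpretation criteria belong in the SAP.* It is right that no test, estimate or stopping decision uses the sentence, and that an SAP not shown may set out the reporting. The absence of such detail here is not the point. The sentence itself makes a positive claim, and nothing else in the article withdraws it.

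**Conclusion.** The concern holds for the sentence as written. Under the article's 3% control rate and 788 evaluable patients per arm, a true reduction at the upper end of the cited range would be non-significant in about 60% of trials, and the planned reduction in about 19%. A non-significant result can carry an interval that includes the planned effect, so it cannot by itself show that benefit is absent or unimportant.

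The severity is moderate. A reader might go further and infer that the trial is undersized or its primary analysis wrong. The documents do not support that: the sample size reproduces for its stated assumptions, and the fault lies only in the conclusion attached to a null result. The 60% figure rests on pairing the 3% planning rate with the 1.7% upper bound and should be quoted with that condition.

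**What to change.** Replace the Discussion sentence. Suggested wording: *A non-significant difference in leak rate will be interpreted from the risk difference and its 95% confidence interval. Absence of a clinically important benefit will be concluded only if the interval excludes a smallest important reduction fixed before unblinding; otherwise the result will be reported as inconclusive.* Null findings on secondary outcomes should be interpreted separately and not used to support a statement about leak.

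The steering committee would need to agree the smallest important reduction before unblinding, and the SAP should carry the same criterion. The change needs no additional patients, procedures or data and leaves the primary test untouched. Its price is that a null conclusion becomes less categorical, and that some results now labelled as no benefit would be reported as inconclusive.

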## Trial status

This article refers to protocol version 4 dated 13 August 2020. The recruitment has begun on 8 October 2020. The anticipated recruitment end date is 7 October 2022.

## Abbreviations

ASA: American Society of Anesthesiologists
BMI: Body mass index
CNIL: Commission nationale de l'informatique et des libertés
CRF: Case report form
DSMB: Data and Safety Monitoring Board
EWL: Excess weight loss
Fr: French
GCP: Good Clinical Practice
GIQLI: Gastrointestinal Quality of Life
LSG: Laparoscopic sleeve gastrectomy
SAE: Serious adverse event
TWL: Total weight loss
